**Results:**

Data processing and analysis will proceed through a series of steps including data normalization, adding information on external factors (weather, traffic conditions), and identifying critical features (variables). Traditional prediction modeling results will be compared with Recurring Neural Network (RNN) approach to produce Driver Behavior Indices (DBIs), and algorithms to classify drivers within age, gender, ethnic group membership, and other potential group characteristics.

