Previous research has focused on older drivers with dementia, but interest in the driving behavior of individuals with MCI is increasing. Few studies have reported the use of continuous, unobtrusive sensors and related monitoring devices for detecting subtle variability in the performance of highly complex everyday activities over time. Eby and colleagues [9] employed in-vehicle technology to monitor driving performance for 2 months. Compared with 26 unimpaired drivers, 17 drivers with early-stage dementia were found to have significantly restricted driving space and were more likely to get lost, even though they had been cleared for driving. In a small sample of 21 unimpaired older adults and 7 with MCI who were followed for 200 days using a sensing device, those with MCI drove fewer miles and fewer of these miles on highways [10].

The Long Road study (2021) is among the first longitudinal studies showing the usefulness of naturalistic data and machine learning techniques to detect MCI and dementia from driving behavior [11]. Among 2977 older drivers studied, 64 were identified as having MCI or dementia through a review of their medical records and annual interview. Age was predictive of MCI and dementia, followed by the percentage of trips traveled within 15 miles of home, race/ethnicity, minutes per trip chain (i.e., length of trips starting and ending at home), minutes per trip, and the number of challenging braking events with deceleration rates 0.35 g. The point of conversion to MCI or dementia could not be determined, at least partly due to the data collection method. Data from our naturalistic, longitudinal study may contribute to identifying these time points.

Similarly, Bayat and colleagues [12] conducted a study using machine learning methods to evaluate the ability of in-vehicle GPS to distinguish drivers with preclinical AD from those without preclinical AD. Using four Random Forest (RF) models with three sets of variables, driving features only, driving features and age, and driving features, age, andAPOE*ε*4 status, it was found that prediction of preclinical AD was 82% using GPS-based driving indicators, 88% using age and driving indicators, and 91% using age, APOE *ε*4 status, and driving.

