## Methods/design

### Objective

The objective of this study is to test an unobtrusive multi-sensor system’s ability to detect cognitive change in older (≥ 65) drivers.

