### Aims

To achieve this goal, the In-Vehicle study has the following aims:Test the ability of a package of in-vehicle sensors to detect cognitive change:Establish baseline cognitive status and driving behaviors.Examine sensor data output for the ability to detect the cognitive change in individual measures, latent constructs, and diagnostic groupings (e.g., change from unimpaired to MCI) over time.Identify cognitive changes that in-vehicle sensors can detect.Identify the sensor system components that best predict these significant changes in cognition.Develop algorithms that can:Translate sensor data into Driving Behavior Indices (DBIs) that are gender, age, and vehicle specific.Examine the accuracy and stability of the DBIs by comparing DBIs generated using exponential smoothing and ARIMA techniques to DBIs that are adjusted for weather and road conditions derived from national and state databases.Provide interpretable indicators of change in DBI and associated decline in the underlying cognitive functions.Evaluate the acceptability to older drivers of the installed systems.Evaluate participants’ response to the sensor system in terms of their awareness of the installed system, obtrusiveness, driver distraction, reported effect on driving behavior, and overall acceptability.

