#### Predictive modeling phase

Two different methods will be used to model the prediction of changes in cognitive functioning followed by a sensitivity analysis. First, a traditional predictive modeling method using a linear mixed effects (LME) model with time varying covariates will be conducted [46]. This LME method will use the processed data aggregated at weekly, monthly, and 3-month intervals along with the features determined by the SHAP analysis. The second method will use a machine learning recurrent neural network (RNN) approach to loop over and pass information from one step to another in the network allowing for the capability to effectively incorporate temporal (time) dependencies in longitudinal data [47]. With RNN, data contains data sequences from k time steps at each time point (ti), input features (Xti), and internal state (memory) from the previous time step (ht(i−1)) allowing for RNN to identify patterns hidden in the sequence of the data not detectible by conventional neural networks [48]. The Driving Behavior Indices (DBIs) algorithms generated will be assessed for ability to predict changes in overall cognitive functioning as well as other specific domains.

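### No stated comparison includes a sensor-free model, so prediction already available from age, demographics and baseline cognition can be credited to the sensors and could not be told apart

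*Protocol article*

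**What the plan says.** The Objective section states the aim as to "test an unobtrusive multi-sensor system’s ability to detect cognitive change in older (≥ 65) drivers". The Predictive modeling phase says how this will be judged: "The Driving Behavior Indices (DBIs) algorithms generated will be assessed for ability to predict changes in overall cognitive functioning as well as other specific domains". No reference level is named against which that ability is measured.

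For the mixed model, the same section says "This LME method will use the processed data aggregated at weekly, monthly, and 3-month intervals along with the features determined by the SHAP analysis". It also mentions time-varying covariates and a later sensitivity analysis, without saying what either contains. The Abstract (Results) sets this traditional model beside the recurrent neural network.

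The Aims add two more comparisons. One is the accuracy and stability of the indices, by "comparing DBIs generated using exponential smoothing and ARIMA techniques to DBIs that are adjusted for weather and road conditions"; the other is to "Identify the sensor system components that best predict these significant changes in cognition". The Aims also ask that the indices be specific to gender, age and vehicle. On earlier evidence from a large cohort of older drivers, the Background reports: "Age was predictive of MCI and dementia, followed by the percentage of trips traveled within 15 miles of home".

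**The concern.** A test of whether sensors detect cognitive change has to separate two things: what the sensor data contribute, and what would be predicted about the same person without them. An older driver, or one who enters with a lower MoCA, may be more likely to decline and may also drive less. An index of miles driven would then predict decline even if it carried nothing beyond age and entry status.

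At stake is the article's main conclusion, that in-vehicle sensing could give early warning of cognitive change. If the only evidence is that the Driving Behavior Indices (DBIs) predict change, a reader cannot tell whether the equipment or the driver's age and starting point did the work.

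**Working it through.** **1. Is there a figure to reproduce?** No. The article states no accuracy target and no accuracy for a model without sensors. The sample size is its only computable design figure, and this point does not depend on it.

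**2. What each stated comparison can show.**

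| Comparison | Where stated | Sensor data on both sides? | What it answers |
|---|---|---|---|
| Linear mixed model against recurrent network | Abstract (Results); Predictive modeling phase | Yes | Which algorithm does better |
| Elastic net against SHAP | Data processing phase | Yes | Which features are kept |
| Smoothing/ARIMA indices against weather- and road-adjusted indices | Aims | Yes | Which construction of the index is more accurate and stable |
| Sensor components against each other | Aims | Yes | Which component ranks highest |
| With and without the driver-facing camera (only if recruitment requires it) | Anticipated challenges | Yes; the other sensors stay in | What one camera adds |

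No row compares sensors with no sensors. The last row shows that the authors accept with/without logic for one component; it is not applied to the whole system.

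**3. Does the article itself give a route by which non-sensor information reaches the indices?** Yes.

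- Age is listed first among the predictors in the large cohort (Background).
- In the cited GPS study, prediction was 82% with driving indicators and 88% with driving plus age. The gain of age over driving is 88 − 82 = 6 points. The gain of driving over age is 88 − x, where x is the age-only figure. The article does not report x, so that gain is unknown. The present plan would leave the same gap.
- The Travel patterns section ties these indices to avoidance that compensates for age-related deficits.
- The Background cites a small study in which drivers who already had MCI drove fewer miles.
- Entry needs a MoCA of 19 or higher and does not require unimpaired status. The battery is meant to sort participants into unimpaired, MCI and early dementia. Baseline status can therefore vary widely.

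**4. Do the stated mitigations supply a comparator?** No.

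- Age-specific indices could mean norming within age, which removes some age signal, or age as an input, which folds its prediction into the index. The article does not say which. Neither touches baseline cognition.
- Reliable change indices and practice-effect corrections refine the outcome.
- The time-varying covariates are unnamed.

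**5. Illustration, with assumed correlations.** This is a between-person, cross-sectional sketch, not the planned longitudinal analysis. Let an index carry no information about change beyond a baseline factor. It correlates a with that factor, and the factor correlates b with change. The index then correlates r = a × b with change. With 460 enrolled and 20% lost, n = 460 × 0.80 = 368. The chance that this marginal correlation reaches two-sided 0.05 follows from z = atanh(r) × √(n − 3):

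- a = 0.2, b = 0.2: r = 0.04, z = 0.040 × 19.1 = 0.76, chance 0.12
- a = 0.4, b = 0.3: r = 0.12, z = 0.121 × 19.1 = 2.30, chance 0.63
- a = 0.5, b = 0.4: r = 0.20, z = 0.203 × 19.1 = 3.87, chance 0.97

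These are powers against a marginal correlation that is truly non-zero. They are not type I error rates. They show that an index with no increment of its own can look predictive, and that how often depends wholly on inputs the article does not give.

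**The case against.** The strongest reply is that this is a condensed article. Covariate lists and reference models are often left to a full protocol or analysis plan, and the unnamed covariates and sensitivity analysis might include them. That is a fair limit: an unseen document could hold a reference model. But the article does state how the system is judged and sets out its comparisons in some detail. The stated rule cannot answer the stated objective, and that goes beyond omitted detail.

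A second reply is that the design is longitudinal. The Braking patterns section describes a driver reacting differently than before, and fixed traits cannot time a shift within one driver. This stands in part. A strictly within-driver analysis would weaken the between-person route. However, the assessment is not restricted to within-driver change, and fixed traits can still enter through differences between persons or in slopes over time.

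A third reply concerns the comparator. The intended users are people whom screening services miss, who have no entry MoCA or diagnosis. For them, an index that tracks existing cognition may be what is wanted. This stands. A reader might infer that success should be defined solely as gain over baseline MoCA and diagnosis; the objective does not support that, so this benchmark should be secondary.

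**Conclusion.** The point holds: every stated comparison has sensor data on both sides, and the indices are judged by absolute prediction. A positive result could not be divided between the sensors and what is known without them.

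Three stronger readings are not supported.

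- A reader might infer that prediction from age and baseline status *will* be credited to the sensors, or that the sensors add nothing. The article gives none of the correlations needed, and its cited cohort also lists several driving features as predictors. *Can be credited, and could not be told apart* is as far as the text goes.
- A reader might infer that mixed model against recurrent network is the only model comparison. It is not; the others simply do not help.
- A reader might take the 0.12 to 0.97 range as a false-positive rate for this study. It rests on assumed marginal correlations in a simpler setting.

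The size of the problem is therefore unknown. The conclusion rests on the article's text alone and assumes that no unseen document names a sensor-free model. The change is worth making before analysis because it determines what the study can say about its objective.

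**What to change.** In the Predictive modeling phase, keep the absolute performance of the DBIs and add a prespecified sensor-free reference model, fitted and scored on the same participants and cognitive outcomes, in two steps:

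- (a) age, sex, education and time since baseline, the benchmark relevant to unscreened drivers;
- (b) the same plus baseline MoCA and baseline diagnosis, as a secondary benchmark.

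Report the gain of reference plus DBIs over each reference, for both the mixed model and the recurrent network. Base any claim that the sensors themselves detect cognitive change on that gain, at least over (a). State also whether age-specific means norming within age or age as an input.

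The information needed is demographic or already part of the baseline assessments, so no visit, test or participant is added. The cost is a few extra model fits and a less favourable headline figure, since an increment is likely to look smaller than raw accuracy.

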#### Driving behavior (normalized driver behavior indices)

Driver Behavior Indices (DBIs) will be estimated from the telematics and vision sensor data. The selection of the DBIs is designed to reflect older drivers’ cognitive function and driving performance. To account for the variation in participants’ driving frequency and mileage, the DBIs will be normalized by the total number of trips, left turns, traveled intersections and/or total mileages. The DBIs will be evaluated for each driver and will be summarized on a daily, weekly, and monthly basis. DBIs are classified into four categories. Examples of DBIs are shown in Table 4.

**Table 4 Tab4:** Driver behavior indices

**Categories**	**DBIs**	**Data Analytics**
**Travel Patterns**	number of trips, miles driven, miles on the highway, miles during the night, daytime, and severe weather, highway miles, etc.	map-matching, data queries, map data, weather data
**Abnormal Driving**	wayfinding, getting lost, ignoring traffic signals and signs, near-collision events, distraction, drowsiness, etc.	machine vision, shortest path, outlier detection, trajectory clustering, frequent graph mining
**Reaction time**	reaction time to traffic light change, front-vehicle taillight, pothole, etc.	vision sensing, data fusion, vibration analysis, machine learning
**Braking Patterns**	eye movements and IMU data at stop signs, traffic signals, tail lights, losing focus, potholes, etc.	signal processing, gaze estimation, data mining, machine vision

#### Travel patterns

DBIs include travel patterns that will be analyzed based on vehicles’ trajectories, combined with map-matching algorithms to relate high-precision positioning data to map data (e.g., traveled road names, the types of roads, and speed limits). The inclusion of map-matching algorithms and weather data is required to analyze trips on freeways and during severe weather conditions, respectively. These travel-pattern-related DBIs are known to be indicative of the changes in older drivers’ cognition and physical functions since they tend to incorporate deliberate avoidance strategies to compensate for age-related deficits [49].

#### Abnormal driving

Advancing abnormal driving pattern detection requires novel multi-attributed spatial network queries for Spatial Network Database (SNDB) due to the heterogeneity of data sources, such as map data, weather, and location of stop signs. For example, queries for identifying abnormal driving patterns need to combine interrelated risk factors under the unified index and analyze these factors based on topological and geospatial reference systems. Furthermore, drivers’ potential route selection can be affected by traffic volume and weather conditions, which also necessitate developing domain specific SNDB queries to achieve an accurate estimation of abnormal traffic patterns. The identification of ignoring traffic signals or stop signs will use the temporally detailed network status (e.g., volume and speed), the number of lanes, and localized spatial information.

#### Reaction time

The reaction time estimation requires the integration of driving scene awareness, eye tracking, and telematics data. The reaction time to traffic lights and taillights will be analyzed by considering various factors, such as distance to the objects and vehicle speed.

#### Braking patterns

Hard-braking-related DBIs will be used to monitor older drivers’ braking patterns and eye movements. Highly-detailed braking-related data will be collected from our telematics and vision sensors. For example, the data fusion of high-precision trajectories, map data, and machine vision will indicate the causes of hard braking events (e.g., stop-and-go conditions at an intersection, tailgating, losing focus, road conditions). Vision sensors will relate hard braking to stop signs or traffic lights, providing detailed glance patterns at an intersection. Importantly, the data analytics of braking patterns must consider whether drivers might be aware of stop signs, traffic signals, and potholes in advance. This can be closely related to memory function. For example, drivers are usually aware of the location of potholes and stop signs in advance when they repeatedly drive the routes in their daily life (e.g., commuting, grocery shopping). If there are changes in their cognitive functioning, they would react differently to traffic signs or potholes than they did prior to the changes.

To address the third study aim, acceptability of the installed sensor systems, the psychometric properties of the DSAQ will be evaluated and differential effects by demographic group (age, gender, ethnic group membership, education) evaluated. Thematic analysis [50] of the interview data on acceptability will provide explanations for the ratings obtained on the DSAQ.

## Ethical considerations

Prior to enrollment, all potential participants receive an explanation of the study including what participation entails and sign a consent approved by the Florida Atlantic University Committee for the Protection of Human Subjects. Study procedures and consent processes were reviewed and approved by the University Committee for the Protection of Human Subjects.

## Anticipated challenges

Several challenges to the successful implementation of this protocol are anticipated. Participation in the study requires a commitment from the participant to attend testing and data retrieval from the installed sensors four times a year for 3 years. A secondary concern is possible. participant hesitation to allow a video camera to focus on the participant’s face. Should this become a problem in the recruitment of participants, otherwise eligible enrollees will be allowed to forego the driver-facing camera, and a comparison of the accuracy of cognitive change detection with and without the driver-facing video data will be added to the data analysis plan.

There may also be some concern about driver information becoming available to insurers. The Certificate of Confidentiality issued by the National Institutes of Health prevents insurance companies from accessing this information without participant consent and should alleviate this concern.

A more technical concern is the ability to assign driving data to the correct individual when a vehicle is driven by more than one person, most likely spouses who share the vehicle. The solution will be to develop and train a facial comparison algorithm to distinguish the two drivers.

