**Method:**

A naturalistic longitudinal design is employed to obtain continuous information on driving behavior that will be compared with the results of extensive cognitive testing conducted every 3 months for 3 years. A driver facing camera, forward facing camera, and telematics unit are installed in the vehicle and data downloaded every 3 months when the cognitive tests are administered.

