### Study eligibility

#### Inclusion criteria

Age 65 and older, a valid driver’s license, evidence of insurance, use of a passenger car or pickup truck, age and education-adjusted Montreal Cognitive Assessment (MoCA) [17] score of 19 or higher, and a willingness to return to one of three testing/installation sites for retesting, data download, and sensor maintenance as needed every 3 months, are all requirements for inclusion. Potential participants must also be able to speak English, Spanish, or Haitian Creole and pass the standard state driver’s license requirements for vision, hearing, strength, and flexibility.

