### Participant recruitment

A community outreach approach to participant recruitment will be led by a dedicated study recruiter with prior research experience. The recruitment effort will begin with networking with representatives of community-based senior services, either at networking events or in individual meetings. This high-level networking is directed to developing connections with organizations that serve the age 55+ segment of the population to elicit invitations to conduct formal and informal information sessions with the older clients/members/residents in their communities, programs, and services. This includes senior living communities, senior day programs, places of worship, and, secondarily, health services. Presentations and discussions with potential participants will be done in English, Spanish, and Haitian Creole. Bilingual research team members will join the study recruiter to conduct the meetings with primarily non-English speaking groups. Printed materials about the study will be available in these languages, as well as information on how to connect with the study team to enroll. Another smaller recruiting effort will be primarily participant-driven. With Institutional Review Board approval, participants who introduce an eligible individual to the study are given an additional gift card for each new enrollee referred.

Individuals who express interest in participation receive further explanation of the study and what participation entails. They are then briefly screened for eligibility, and an appointment is made. On the first visit, further explanation of the study is provided, consent is obtained, eligibility is confirmed, and baseline tests are administered. A sensor installation team places the telematic and video sensors in the participants’ vehicle once consent is obtained and eligibility confirmed.

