#### Enrollment procedures

Older drivers who express an interest in participation will receive an explanation of the study and the activities that participation entails. They will then be screened for eligibility and proceed to the first set of assessments. An installation team will place the telematics and video sensors in participants’ vehicles while the cognitive tests are administered.

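### Trip and mileage indices cover only the instrumented vehicle but are read as the person's driving; a changing share of driving in another vehicle is not recorded

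*Protocol article*

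**What the plan says.** The Method paragraph of the abstract gives the unit of installation: "A driver facing camera, forward facing camera, and telematics unit are installed in the vehicle". Under Participant recruitment, the installation team "places the telematic and video sensors in the participants’ vehicle once consent is obtained" and eligibility is confirmed. Enrollment procedures has the plural: "An installation team will place the telematics and video sensors in participants’ vehicles while the cognitive tests are administered". Inclusion criteria asks only for "use of a passenger car or pickup truck", and Exclusion criteria adds only that a person without a vehicle to drive is excluded. Neither requires that the fitted vehicle be the sole or main one.

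Table 4, under Driving behavior (normalized driver behavior indices), lists as travel-pattern indices "number of trips, miles driven, miles on the highway", as well as night-time miles. The text above it sets the level at which they are read: "The DBIs will be evaluated for each driver and will be summarized on a daily, weekly, and monthly basis". The Travel patterns section gives the interpretation: "These travel-pattern-related DBIs are known to be indicative of the changes" in older drivers' cognition and physical function, because such drivers tend to avoid certain driving on purpose. The abstract's Background names fewer and shorter trips among possible early changes.

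Anticipated challenges raises the attribution problem as how to "assign driving data to the correct individual when a vehicle is driven by more than one person". Its solution is an algorithm that tells two drivers of the same vehicle apart by face.

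**The concern.** The measurement belongs to a vehicle and the interpretation to a person. The two agree only if the participant's driving stays in the fitted vehicle, or if the part done elsewhere stays constant. The article deals with extra drivers in the fitted vehicle but not with the participant's own driving outside it. It describes no question or log on other vehicles and no rule for a change of main vehicle.

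Over 3 years a participant may begin to use a spouse's car for longer trips, or return to the fitted car after using another. The first looks like restricted driving, and the second can hide real restriction. At stake is the validity of the travel-volume indices as predictors of cognitive change, and so part of the aim of identifying which sensor components predict best.

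**Working it through.** The article states no figure on this point, so there is none to reproduce. The check has two parts.

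**1. Could anything described in the article catch the problem?**

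- Facial comparison (Anticipated challenges) works on images from the fitted vehicle and cannot see a trip made in another one.
- Normalization (Driving behavior section) divides by trips, left turns, intersections or mileage. These totals come from the same recorded data, so dividing by them cannot restore unrecorded driving.
- Standardization for speed and trip duration (Data processing phase) likewise works on recorded trips only.
- Vehicle-specific indices (Aims) calibrate an index to a vehicle. They do not recover driving done elsewhere.

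**2. Size of the error for one person.** Let T be true driving and s the share done in an uninstrumented vehicle. The article gives no s, so the values 10%, 25% and 50% are assumptions.

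Recorded driving = T × (1 − s). With T unchanged, the ratio of recorded driving after to before is (1 − s_after) / (1 − s_before).

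Starting from s = 0 and T = 100:

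| Share moved | Recorded | Apparent change | True change |
|---|---|---|---|
| 10% | 90 | −10% | 0 |
| 25% | 75 | −25% | 0 |
| 50% | 50 | −50% | 0 |

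This is exact for trips. For miles it holds if the moved trips are of average length; if longer trips move, recorded miles fall by more.

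- **Constant share.** With s = 25% throughout, the ratio is 0.75 / 0.75 = 1. The level is too low, but there is no within-person trend.
- **Masking.** Suppose s goes from 25% to 0 while true driving falls from 100 to 75. Recorded driving is 100 × 0.75 = 75 before and 75 × 1 = 75 after, so a true 25% fall is invisible.
- **Per-mile event rate.** Assume 5 events per 100 miles and a random 25% of driving moved. Recorded events are 5 × 0.75 = 3.75 over 75 miles, still 5 per 100. The rate is unaffected.
- **Selective move.** Assume 30 of 100 true miles are highway miles and that a share s of those highway miles alone moves. The recorded highway share is 30(1 − s) / [70 + 30(1 − s)]: 27/97 = 27.8% for s = 10%, 22.5/92.5 = 24.3% for 25%, and 15/85 = 17.6% for 50%, against a true 30%. A proportion is therefore also distorted when the moved trips differ in type, in the direction of highway avoidance.

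**The case against.** The strongest reply is that cognition is measured independently, by the test battery and the algorithmic diagnosis. The DBIs are candidate predictors, and elastic net and SHAP are there to find the useful ones. A change in mileage unrelated to cognition is then noise in a predictor and tends to weaken that feature's association. This stands. A reader might infer that a participant who switches vehicle is recorded as having declined cognitively, or that restricted driving is the signal on which the study rests. The documents support neither: no outcome is altered, and travel patterns are one of four categories, beside abnormal driving, reaction time and braking patterns.

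It can also be said that a condensed article leaves operational detail to the full protocol, that the list of challenges does not claim to be complete, that the quarterly forms are not shown, and that a single fitted vehicle is inferred from the singular wording. All of this is fair. The plural under Enrollment procedures, however, goes with plural participants and does not say that every vehicle is fitted. The article also chose to present the attribution problem with its solution, and that solution covers one direction only. An analysis plan cannot recover what was not collected.

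Finally, a deployed in-vehicle system would meet vehicle switching too, so a naturalistic test should arguably include it. That is a reason to record switching, so that performance with and without it can be reported, rather than to leave it unknown.

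**Conclusion.** The point holds as a cheap improvement. As described, a change over time in the share of driving done in an uninstrumented vehicle enters the travel-volume DBIs as a spurious change. The recorded data alone cannot separate it from a real change in the person. Starting from zero, recorded trips fall by exactly the share moved. Per-mile and per-trip indices are affected only when the moved trips differ in type.

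The conclusion assumes that installation is limited to one vehicle per participant and that the share changes for some participants. The documents do not say how many. It would therefore go too far to claim a particular loss of specificity, power or predictive accuracy: none can be computed from the article. Nor does the article give any basis for saying that the error falls unevenly across demographic groups.

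**What to change.** - **Installation.** State that the sensors go into the vehicle the participant drives most.
- **Data collection.** At each existing quarterly visit, record whether the main vehicle changed and roughly what share of driving since the last visit was in other vehicles.
- **Analysis.** Carry this as a time-varying covariate or flag for the travel-volume DBIs in both the linear mixed effects and the recurrent neural network models.
- **Sensitivity analysis.** Repeat the analysis in participants or quarters with all, or almost all, driving in the fitted vehicle.

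Setting quarters to missing in the main analysis above a fixed limit, such as 25%, is not advised. The limit would be arbitrary, and because it would rest on self-report, the resulting missingness could be related to the cognitive outcome.

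The cost is one short item at visits already scheduled and one extra variable. The drawback is that recall may be less accurate in participants whose cognition is declining, so the item should be treated as approximate. If the full protocol or visit forms already collect this, a sentence in Anticipated challenges saying so would be enough for the data-collection part.
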